### Eligibility criteria {10}

The study population will be composed of children living in the catchment area of 11 health centers of the Nara district where the study will be taking place. Inclusion criteria include (a) age between 6 and 59 months, (b) MUAC ≥125 mm, (c) WAZ <−3, (d) living in the study catchment area, and (e) expects to be able to continue follow-up visits for next 6 months. Children will not be included in the trial if they have (a) nutritional edema, (b) known peanut or milk allergy, (c) severe illnesses requiring inpatient level treatment (according to CMAM guidelines), (d) medical condition affecting food intake (lip and palate cleft, handicap etc.), and (e) has already taken part in the study.

### Who will take informed consent? {26a}

Eligibility for the study will be assessed at the research site by the research staff who are not routine health staff but are employed specifically to conduct the study. Once a child has been screened eligible at the research site, their caregiver will be informed about the study in the local languages by one of the 5 research personnel present at the study site speaking the caregivers’ language. Each research team is composed of a supervisor, 2 nurses, and 2 polyvalent workers. Once the caregiver has been given time to ask questions, they will be invited to participate, and if they consent, asked to sign or thumbprint the consent form.

### Additional consent provisions for collection and use of participant data and biological specimens {26b}

Participants will be asked for their consent to make de-identified data publicly available and use it for further research purposes.

## Interventions

### Explanation for the choice of comparators {6b}

The simplified treatment will be compared both to the current WHO-recommended standard treatment as well as to no treatment. The standard protocol is considered as the reference practice in the field and is needed as a comparator in order to judge whether the simplified protocol results in no worse outcomes compared to the standard treatment. The control arm is needed to establish whether simplified or any treatment actually results in improvement in nutritional status both in the short and in the long term.

### Intervention description {11a}

Intervention will start on the same day as children are confirmed eligible and caregivers have given their consent for participation. Children in the control group will not receive any nutritional treatment nor any other equivalent value non-food item. Children randomized to the simplified arm will all receive a nutritional treatment until being discharged. This nutritional treatment will consist of 1 sachet of RUTF per day for a maximum of 12 weeks or until reaching a WAZ ≥−3 for 2 consecutive visits. Children randomized to the standard arm will be categorized into 3 sub-groups: (1) those with a WHZ <−3, (2) those with a WHZ between −3 and <−2, and (3) those with WHZ ≥ −2. Children in the first sub-group will receive a weight-based RUTF dose that aims at providing 200 kcal/kg/day. The second sub-group will receive 1 sachet of RUTF per day. Both first and second sub-groups will be treated until WHZ ≥ −2 for 2 consecutive visits or for a maximum of 12 weeks. The third sub-group will receive no treatment. All children irrespective of their arm or sub-group will be followed up fortnightly until 12 weeks and then monthly until 24 weeks post-enrolment.

Exit criteria from treatment ire followed in the 2 intervention arms: standard and simplified treatment arms. Children in the control arm will not have exit criteria as they do not receive treatment and are only followed up.

Six exit categories exist from treatment: (1) recovery; (2) defaulting defined as missing 2 consecutive appointments at the treatment facility; (3) non-response, defined as not reaching the recovery criteria within 12 weeks; (4) died, defined as those cases of children that die during the trial, regardless of the reason of death; (5) transfer to inpatient care, defined as those cases that develop medical complications, as per the national protocol, and require inpatient treatment during the trial; (6) developing a MUAC <125 mm or edema.

Recovery is defined differently for children in the simplified and standard arm. In the simplified arm, recovery is defined as reaching a WAZ ≥−3 for 2 consecutive visits. In the standard arm, recovery is defined as reaching a WHZ ≥−2 for 2 consecutive visits. See Table 1 for the differences between arms.

**Table 1 Tab1:** Differences in intervention and end of intervention criteria between study arms

PROCEDURES	Control arm	Simplified treatment arm	Standard treatment arm
Treatment provided	None	1 sachet of RUTF/day	Depending on the WHZ score: • WHZ <−3: 200 kcal of RUTF/kg/day • WHZ between −3 and −2: 1 sachet of RUTF/day • WHZ ≥−2: no treatment
Recovery criteria from treatment	None	WAZ >−3 on 2 consecutive visits	WHZ ≥−2 on 2 consecutive visits

All other exit categories except for MUAC <125 mm or edema or died continue in the study unless the caregiver is not willing to do so. All children requiring inpatient-level care will be referred to the health center’s head nurse or doctor for them to prepare a formal referral of the patient to inpatient care.

Children will be classified in 5 different categories at the exit from the study: (1) finished 6-month follow-up, (2) developed MUAC <125 mm or edema during follow-up and was referred to routine treatment, (3) abandoned study, (4) lost-to-follow-up, (5) died. Abandoned will be defined as those who do not come back to study visits but who have been contacted to confirm the child is still alive. Lost-to-follow-up will be defined as those who do not come back to study visits and who have not been reached to confirm whether the child is still alive.

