### Objectives {7}

The primary objective of this study is to assess whether therapeutic feeding with a simplified protocol results in 1) superior nutritional outcomes compared to no therapeutic feeding and 2) non-inferior nutritional outcomes compared to the WHZ and weight-based dosing regimen currently used in CMAM treatment, 2 months after diagnosis among children aged 6–59 months with MUAC ≥125 mm and WAZ <−3.

The secondary objective of this study is to assess whether therapeutic feeding with a simplified protocol results in (1) sustainably superior nutritional outcomes compared to no therapeutic feeding and (2) sustainably non-inferior nutritional status compared to the WHZ and weight-based dosing regimen currently used in CMAM treatment, 6 months after diagnosis among children aged 6–59 months with MUAC ≥125 mm and WAZ <−3.

Additional objectives include assessing whether the simplified protocol results in fewer children presenting negative outcomes compared to no treatment and non-inferior treatment outcomes compared to standard treatment.

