### Outcomes {12}

Both primary and secondary outcomes will be reported for all 3 arms at both 2 (primary endpoint) and 6 months (secondary endpoint) post-enrolment. The primary outcome is the mean WAZ of children. WAZ has been shown to be strongly associated with mortality and thus acts as a proxy of the ultimate goal of reducing child mortality. Increase in WAZ can be both related to the increase in HAZ or WHZ, which is an added value as it enables appreciating and aggregating both outcomes that are positive. As a continuous measure, WAZ is well adapted to capture the response to treatment among the study population as it will more easily capture smaller benefits of treatment compared to categorical outcomes.

Secondary outcomes include (a) proportion of children with WAZ <−3, (b) mean MUAC of children, (c) mean WHZ and HAZ, (d) proportion of children with WHZ <−3 or HAZ <−3, (e) mean skinfold thickness measures and mean skinfold thickness per age percentile, (f) mean fat-free mass and fat mass, fat-free mass index and fat mass index, (g) mean hemoglobin measure, and (h) change in all these outcomes from enrolment to endpoint. In addition, the proportion of children exiting the study at any time point due to a MUAC <125 mm or edema or diseased or hospitalized will be reported across arms. Finally, treatment outcomes will be reported for the 2 treatment groups including the percent recovered, defaulted, non-response, transferred to inpatient care, and died. The study exit status will be reported for all 3 arms including completion of the 6-month follow-up, developed a MUAC <125mm or edema during the study, abandoned study, lost-to-follow-up, and died.

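### Percent recovered and non-response rest on different criteria in the two treatment arms, so they cannot support the additional objective of non-inferior treatment outcomes

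*Protocol article*

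**What the plan says.** **Definitions.** Intervention description {11a} states that "Recovery is defined differently for children in the simplified and standard arm" and gives each arm its own criterion: "In the simplified arm, recovery is defined as reaching a WAZ ≥−3 for 2 consecutive visits" and "In the standard arm, recovery is defined as reaching a WHZ ≥−2 for 2 consecutive visits". Table 1 repeats the split in its row "Recovery criteria from treatment", although it prints a strict inequality for WAZ where the text allows equality; those two places must be reconciled. The fourth-to-last link in the chain is non-response: "non-response, defined as not reaching the recovery criteria within 12 weeks". It therefore also means different things in the two arms.

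**Who is in the standard arm.** Eligibility criteria {10} require WAZ <−3 and MUAC ≥125 mm and set no WHZ limit. The standard arm is divided by WHZ at entry, and of those with WHZ ≥−2 the protocol says: "The third sub-group will receive no treatment".

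**What the percentages are for.** Objectives {7} lists, as an additional objective, "non-inferior treatment outcomes compared to standard treatment". Outcomes {12} uses the same term: "treatment outcomes will be reported for the 2 treatment groups including the percent recovered", followed by default, non-response, transfer and death. Statistical methods {20a} says that treatment outcomes will be described by count and percentage.

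**The concern.** An objective phrased as non-inferiority needs an outcome that means the same thing in both arms. Here two of the five treatment outcomes do not.

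No simplified-arm child can be above the WAZ threshold at entry, because WAZ <−3 is an entry criterion. Some standard-arm children are above the WHZ threshold at entry, and exactly those children are not fed. They can complete the two-visit rule at the first fortnightly visit if enrolment counts as a visit, or at the second if it does not, without any treatment.

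At stake is a reader of the results setting the two recovery percentages side by side, under an objective that invites it, and concluding that one protocol works better or no worse. The same data could lead to either conclusion.

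**Working it through.** **1. What the plan's figures cover.** The protocol gives no figure for percent recovered or non-response. Its only non-inferiority margin, in Sample size {14}, is 0.2 for mean WAZ. That calculation reproduces: n = 2 × 1.1² × (1.960 + 0.842)² / 0.2² ≈ 475 per group, and 475 / (1 − 0.20) ≈ 594 per arm. Nothing in it concerns recovery.

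**2. The denominator alone moves the result.** Let f be the share of standard-arm children entering at WHZ ≥−2, and g the share of the fed remainder who reach WHZ ≥−2. Suppose the unfed children stay above the threshold. Percent recovered in the standard arm is then:

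- f + (1 − f)g if the unfed children are counted as recovered
- g if they are left out
- (1 − f)g if they stay in the denominator but not the numerator

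The protocol gives neither f nor g. Taking f = 0.4 and g = 0.5 as an example, the same children give 0.4 + 0.6 × 0.5 = 70%, or 50%, or 0.6 × 0.5 = 30%. Leaving them out also compares the whole simplified arm with only the wasted part of the standard arm, which is not the randomised comparison.

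**3. The criterion moves it too, even with no treatment difference.** Assumptions (none is in the protocol): identical children and identical growth in both arms; entry WAZ equal to −3 minus an exponential with mean 0.4; entry WHZ with SD 0.8 and mean −2.5, −2.0 or −1.5; a gain of 0.3 (SD 0.3) on both indices; the threshold checked at a single visit. Differences are simplified minus standard, in percentage points.

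| Entering at WHZ ≥−2 | WAZ rule (simplified) | WHZ rule, whole standard arm | Difference | WHZ rule, fed children only | Difference |
|---|---|---|---|---|---|
| 27% | 46.6% | 40.8% | +5.8 | 20.5% | +26.1 |
| 50% | 46.6% | 63.7% | −17.1 | 29.9% | +16.7 |
| 73% | 46.7% | 82.6% | −35.9 | 38.6% | +8.1 |

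With zero mean gain, the WAZ rule gives 20% against 28%, 50% or 72% for the whole standard arm.

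**4. Other assumptions, with the two-visit rule.** Six fortnightly visits; entry WAZ equal to −3 minus an exponential with mean 0.45; a 12-week WAZ gain of 0.4 (SD 0.4); a WHZ gain 1.2 times as large; entry WHZ SD 0.8. With 31%, 50% or 69% entering at WHZ ≥−2, the WAZ rule gives 46% each time. The WHZ rule gives 50%, 68% or 82% over the whole arm (differences −4, −22, −36) and 29%, 37% or 44% among wasted children only (+17, +9, +2).

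The true difference is zero throughout steps 3 and 4. The apparent difference changes sign with the handling of the unfed children, and in step 3 also with the entry WHZ mix.

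**The case against.** **No test is planned.** Statistical methods {20a} only describes treatment outcomes by count and percentage, apart from the mixed models, with no test, margin or power. This stands. A reader might infer that the trial will formally test non-inferiority of recovery; the protocol does not support that. But the objective is still worded as non-inferiority on treatment outcomes, and the percentages are what a reader would hold against it.

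**Other treatment outcomes are sound.** Default, transfer and death have one definition in both arms. This stands, so the objective is only partly affected.

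**Threshold crossing without treatment is observed.** A reader might infer from the control arm's lack of exit criteria that it is not. That is not so: Outcomes {12} reports the proportion with WAZ <−3 in all three arms at 2 and 6 months, and since every child enters below −3, its complement is the share above the simplified arm's threshold. Only the two-visit, 12-week form is missing.

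**The unfed children may not be meant to count.** The categories are exits from treatment, and the reason given for exempting controls, that they are not treated, fits these children too. That is a fair reading, but the text applies exit criteria to the standard arm without excepting them. Leaving them out does not rescue the comparison either, as step 2 shows.

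**Exit rules belong to the strategies compared.** Agreed. Describing exits against each strategy's own rule is reasonable; using them as a comparative endpoint is not.

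**Conclusion.** The point holds for percent recovered and non-response only. As defined, they cannot support the additional objective of non-inferior treatment outcomes, however the unfed standard-arm children are handled. This follows from the definitions and needs no assumption.

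The size and direction do need assumptions. The protocol gives neither the entry WHZ mix nor the expected growth by index, so the figures above show that the percentages can mislead, not by how much or which way they will. A reader might infer that the bias favours the standard arm; the illustrations do not support a fixed direction.

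Nor does the point reach the main conclusions. Mean WAZ, the proportion with WAZ <−3, default, transfer and death are commonly defined and unaffected. It is worth correcting because the correction is cheap, but it does not threaten the primary result.

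**What to change.** Leave the treatment-exit rules as they are and change the outcome wording:

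1. In Objectives {7} and Outcomes {12}, rest the recovery part of the additional objective on one criterion, computed from visit anthropometry in every randomised child in all three arms: WAZ ≥−3 on two consecutive visits by week 12, or simply the complement of existing outcome (a). If the 12-week form is chosen, state one rule, the same in each arm, for children who leave the study earlier.
2. Add, as a supplementary outcome among children with WHZ <−2 at enrolment in all arms, WHZ ≥−2 on two consecutive visits by week 12. Enrolment WHZ precedes treatment, so this remains a randomised comparison.
3. State that the arm-specific recovery and non-response percentages are programme description, not to be compared between arms, and show standard-arm children who were never fed in a separate row.

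The cost is a small amount of extra analysis. Weight and height are already measured in all children at every visit, so no new data, visits or change to treatment are needed. The wording should be settled before the intervention code is released to the investigators.

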### Criteria for discontinuing or modifying allocated interventions {11b}

There will be no criteria for changing treatment once allocated to a treatment arm. However, participants can withdraw their consent to participate in the study at any moment. Children developing medical complications will be referred to inpatient care where study-independent medical and nutritional treatment may be administered.

### Strategies to improve adherence to interventions {11c}

Upon RUTF distribution, caregivers will be reminded that the product is only intended to be given to the participating child and not to anyone else and advised on the correct daily dosing of the product. Consumption of RUTF will be monitored through questions on intake and by asking caregivers to return empty sachets at each visit.

### Relevant concomitant care permitted or prohibited during the trial {11d}

Any illnesses identified during study visits or outside of study visits in routine health care will be treated as per the Malian national protocol for the treatment of childhood illnesses. No prohibitions for concomitant care are applied. Children developing a MUAC <125mm or edema will be discharged from the study and referred to routine simplified treatment available at all study sites and throughout the district.

### Provisions for post-trial care {30}

Post-trial care can be sought via the routine health care available throughout the district. Any unexpected health problems that can be ascribed to participation in the study will be covered through a patient insurance which IRC has secured specifically for this trial.

### Outcomes {12}

Both primary and secondary outcomes will be reported for all 3 arms at both 2 (primary endpoint) and 6 months (secondary endpoint) post-enrolment. The primary outcome is the mean WAZ of children. WAZ has been shown to be strongly associated with mortality and thus acts as a proxy of the ultimate goal of reducing child mortality. Increase in WAZ can be both related to the increase in HAZ or WHZ, which is an added value as it enables appreciating and aggregating both outcomes that are positive. As a continuous measure, WAZ is well adapted to capture the response to treatment among the study population as it will more easily capture smaller benefits of treatment compared to categorical outcomes.

Secondary outcomes include (a) proportion of children with WAZ <−3, (b) mean MUAC of children, (c) mean WHZ and HAZ, (d) proportion of children with WHZ <−3 or HAZ <−3, (e) mean skinfold thickness measures and mean skinfold thickness per age percentile, (f) mean fat-free mass and fat mass, fat-free mass index and fat mass index, (g) mean hemoglobin measure, and (h) change in all these outcomes from enrolment to endpoint. In addition, the proportion of children exiting the study at any time point due to a MUAC <125 mm or edema or diseased or hospitalized will be reported across arms. Finally, treatment outcomes will be reported for the 2 treatment groups including the percent recovered, defaulted, non-response, transferred to inpatient care, and died. The study exit status will be reported for all 3 arms including completion of the 6-month follow-up, developed a MUAC <125mm or edema during the study, abandoned study, lost-to-follow-up, and died.

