### Sample size {14}

Based on previous work on a similar population and similar intervention [48] we assumed a similar response to treatment and a similar SD for WAZ. Thus, for looking at hypothesis 1, we set an objective of measuring a meaningful impact of the simplified treatment (compared to no treatment) at a difference of 0.4 *z*-scores in WAZ. For calculating the sample size, we applied (a) SD of 1.1 WAZ, (b) power of 80%, (c) probability of type 1 error of 2.5%, and (d) obtained a sample size of 146 per group. Accounting for not having measures for 30% of children (particularly in the control arm) at 2 months due to (a) defaulting, lost-to-follow-up, or death (10%) or (b) development of MUAC <125 mm or edema (20%), we estimated needing 209 children in both control and simplified treatment arms each.

For looking at hypothesis 2 we set an objective of measuring a meaningful non-inferiority margin of 0.2 *z*-scores in WAZ. For calculating the sample size, we applied (1) SD of 1.1 WAZ, (2) non-inferiority margin of 0.2, (3) power of 80%, and (4) probability of type 1 error of 2.5% and obtained a sample size of 475 per group. Accounting for not having measures for 20% of children at 2 months due to (a) defaulting, lost-to-follow-up, or death (10%) or (b) development of MUAC <125 mm or edema (10%), we need 594 children in simplified and standard treatment arms each.

To be able to explore both hypotheses, we need 209 children in the control arm and 594 children in both the simplified and standard treatment arms meaning a total of 1397 children.

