#### Body composition

Body composition will be measured both by measuring skinfold thickness as well as the bioelectrical impedance. Body composition will be measured at enrolment and at 8 and 24 weeks from enrolment.

Skinfold thickness will be measured with the GIMA code 27346 device that gives an electronic reading of the result with 1mm precision. Skinfold thickness measures will be performed at the sub-scapular and triceps levels from the right side of the child with the child in a sitting position. Repeated measures will be performed for each site altering the measurer and the assistant. Bioelectrical impedance will be analyzed with the BodyStat 500 device that provides measurements for the resistance, reactance, and phase angle. A repeat measurement will be performed.

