## Statistical methods

### Statistical methods for primary and secondary outcomes {20a}

In reporting the trial outcomes, we will follow the CONSORT 2010 statement for reporting parallel group randomized trials [50]. This will include reporting participant flow through the trial as per the CONSORT guidance [50]. All statistical analysis will be done using STATA® software or similar. Baseline characteristics will be reported by the study arm. Linear mixed models will be fitted to analyze the primary outcome and all continuous outcomes while logistic mixed-effects models will be fitted for binary or categorical outcomes. Random effects will include participants, study sites, and study teams. Adjustment for block randomization will be applied by means of random effects. Adjustment for confounders such as age and sex and outcome at enrolment will be included. To investigate effect modification, two-way interactions between intervention group and age group, sex, and degree of undernutrition (WHZ, WAZ and HAZ categories) will be assessed.

Anthropometric outcomes at 2 and 6 months post enrolment will be analyzed by adjusting for the exact number of days from enrolment to the measurement date. In addition, the treatment outcomes will be described for the 2 treatment groups, and the study exit status for all 3 study groups using count and percentage.

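### Comparing arms on mean skinfold-for-age percentile can under-weight response in lean children and lose power; the z-score from the same measurements avoids this at no cost

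*Protocol article*

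**What the plan says.** Protocol article, Outcomes {12}, item (e), lists "mean skinfold thickness measures and mean skinfold thickness per age percentile" as a secondary outcome at 2 and 6 months. Item (h) adds "change in all these outcomes from enrolment to endpoint", so change in the percentile is an outcome too. Item (f) lists "mean fat-free mass and fat mass, fat-free mass index and fat mass index".

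Under Body composition: "Skinfold thickness measures will be performed at the sub-scapular and triceps levels". Under Statistical methods {20a}: "Linear mixed models will be fitted to analyze the primary outcome and all continuous outcomes", with adjustment for age, sex and the outcome at enrolment. The arm contrast for this outcome is therefore a difference in mean percentile.

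Weight-for-age, weight-for-height and height-for-age are all analysed as z-scores. No skinfold-for-age z-score is listed. The eligibility list reads "b) MUAC ≥125 mm, (c) WAZ <−3"; nothing in it refers to skinfold. The article gives no skinfold mean, SD, reference or expected effect, and claims no power for any skinfold outcome.

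**The concern.** A percentile is a non-linear function of the z-score that is steep near the median and almost flat in the tails. When percentiles are averaged, the same gain in z counts for many points in a child near the reference median and for a fraction of a point in a very lean child. The arm difference becomes a weighted average of the children's responses, and below the median the weights fall as leanness increases.

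In a trial of severely underweight children this matters if their skinfolds are low as well. The analysis could then show little difference although the leanest children had responded. The percentile is also bounded at 0 and becomes skewed near that bound, which suits a linear model less well than a z-score does. What is at stake is the sensitivity of one secondary outcome, not the trial's main conclusions.

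**Working it through.** **1. Numbers in the planned comparisons (Sample size {14}; these are for WAZ).**
- Superiority: 2 × 1.1² × (2.241 + 0.842)² / 0.4² ≈ 144 per group with two-sided alpha 2.5%, against the stated 146. Then 146 / 0.70 → 209.
- Non-inferiority: 2 × 1.1² × (1.960 + 0.842)² / 0.2² ≈ 475 per group, as stated. Then 475 / 0.80 → 594.
- Total: 209 + 2 × 594 = 1397.

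The control comparison would thus have about 146 measured control children against about 475 in the simplified arm. This point leaves these sizes unchanged.

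**2. Compression of the scale.** Take percentile = 100 × Φ(z). The gain from +0.4 z is 100 × [Φ(z + 0.4) − Φ(z)]. The 0.4 is borrowed from the WAZ target ("at a difference of 0.4 *z*-scores in WAZ") and is only an assumption for skinfold.

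| Starting z | Percentile before | Points gained |
|---|---|---|
| 0 | 50.0 | 15.5 |
| −1 | 15.9 | 11.6 |
| −2 | 2.3 | 3.2 |
| −3 | 0.13 | 0.33 |

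The same gain counts about 35 times more from −1 than from −3 (11.6 / 0.33), and about 47 times more from 0 than from −3 (15.5 / 0.33).

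**3. Power in the control comparison.** Assumed, since the article gives none of it: enrolment skinfold z normal with SD 1, SD of change 0.6, a uniform gain of 0.15 z, 146 against 475 children, adjustment for the enrolment value, two-sided 5%. Power is by simulation.

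| Mean enrolment z | Power, z-score | Power, percentile |
|---|---|---|
| −2.5 | 0.76 | 0.34 |
| −2 | 0.78 | 0.46 |
| −1 | 0.76 | 0.63 |
| 0 | 0.74 | 0.69 |

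Check on the z-score column, which should not depend on the mean: the standard error is 0.6 × √(1/146 + 1/475) = 0.0568, 0.15 / 0.0568 = 2.64, and Φ(2.64 − 1.96) ≈ 0.75. The spread of 0.74 to 0.78 is simulation error.

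With a larger gain the loss shrinks. Percentile power at 0.3 z is 0.89 at mean −2.5 and 0.96 at −2. At 0.4 z it is 0.99 at −2.5 and above 0.99 from −2 upward.

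**4. If the gain is not uniform.** This is a simpler calculation without enrolment adjustment (146 against 475, SD 1.0), with a gain of 0.6 z in the leaner half only. Power on the z-score is 91%. On the percentile it is 57% at mean −1, 29% at −1.5 and 13% at −2. At mean 0 the order reverses: 96% on the percentile.

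**The case against.** The strongest reply is that the premise is not in the document. A reader might infer that enrolling at WAZ below −3 puts these children in the lower tail of skinfold-for-age, so that the outcome mostly ignores the leanest children. The article does not support that. Children are selected on weight-for-age, not on skinfold. The MUAC criterion removes those with small arms. The Outcomes section links WAZ to both height-for-age and weight-for-height, so a low WAZ may reflect short stature. The standard arm provides for children with WHZ of −2 or above, so non-wasted children are expected. This objection stands: where the skinfold distribution lies is unknown, and the loss is conditional.

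A reader might also infer that the trial's evidence on fat regain rests on the percentile. It does not. Raw skinfold is reported in the same item and, under {20a}, analysed with adjustment for age and sex. Fat mass and fat mass index are reported as well, and interactions and subgroups by degree of undernutrition are planned. Nor is it right that every other standardised measure is a z-score: fat mass index and fat-free mass index are height-standardised and not given as z-scores.

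Third, the power loss depends on a small assumed effect, and a superiority test at 475 against 475 is not a planned comparison. That is why the figures above use 146 against 475 and show larger gains too.

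Finally, the percentile reference and any transformation may be specified in the full protocol or analysis plan. That is fair for the details, but the scale itself, a mean percentile, is fixed in the article.

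**Conclusion.** The point holds as a conditional and minor one. The plan commits to an average of percentiles, and the compression is arithmetic fact. Its effect depends on three unstated things: where the children's skinfold z-scores lie, how large the gain is, and who gains.

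For a uniform 0.15 z gain in the control comparison, the loss runs from about 5 points of power at mean 0 (0.74 against 0.69) to about 42 at mean −2.5 (0.76 against 0.34). At 0.4 z it practically vanishes. If the benefit falls mainly on the leaner half, the loss is already large at a mean of −1.

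The z-score was at least as efficient in every uniform-gain setting tried. The one setting that favoured the percentile was a mean of 0 with gain only in the leaner half. The primary outcome, the sample size and the main conclusions are unaffected.

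**What to change.** In Outcomes {12}, item (e), replace the mean percentile as the analysed outcome with mean triceps and mean subscapular skinfold-for-age z-score. Compute them from the same measurements and the same reference, and analyse them in the planned mixed model with adjustment for the enrolment z-score, which {20a} already provides for. Item (h) then applies to change in z-score. Keep raw skinfold as planned and show percentiles in a descriptive table only.

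The cost is one line of outcome wording and the matching line in the analysis code. No new measurements, visits or children are needed.
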